## Abstract

**Background:**

Day care center attendance has been recognized as a risk factor for acquiring gastrointestinal and respiratory infections, which can be prevented with adequate hand hygiene (HH). Based on previous studies on environmental and sociocognitive determinants of caregivers’ compliance with HH guidelines in day care centers (DCCs), an intervention has been developed aiming to improve caregivers’ and children’s HH compliance and decrease infections among children attending DCCs. The aim of this paper is to describe the design of a cluster randomized controlled trial to evaluate the effectiveness of this intervention.

**Methods/design:**

The intervention will be evaluated in a two-arm cluster randomized controlled trial among 71 DCCs in the Netherlands. In total, 36 DCCs will receive the intervention consisting of four components: 1) HH products (dispensers and refills for paper towels, soap, alcohol-based hand sanitizer, and hand cream); 2) training to educate about the Dutch national HH guidelines; 3) two team training sessions aimed at goal setting and formulating specific HH improvement activities; and 4) reminders and cues to action (posters/stickers). Intervention DCCs will be compared to 35 control DCCs continuing usual practice. The primary outcome measure will be observed HH compliance of caregivers and children, measured at baseline and one, three, and six months after start of the intervention. The secondary outcome measure will be the incidence of gastrointestinal and respiratory infections in 600 children attending DCCs, monitored over six months by parents using a calendar to mark the days their child has diarrhea and/or a cold. Multilevel logistic regression will be performed to assess the effect of the intervention on HH compliance. Multilevel poisson regression will be performed to assess the incidence of gastrointestinal and respiratory infections in children attending DCCs.

**Discussion:**

This is one of the first DCC intervention studies to assess HH compliance of both caregivers and children, as well as the incidence of gastrointestinal and respiratory infections in children, as outcome measures. When an effect of the intervention on improving HH compliance and/or reducing incidence of infections is shown, (inter)national dissemination of the intervention in other DCCs may be considered.

**Trial registration:**

Netherlands trial registry:
NTR3000

## Background

Attendance at child day care centers (DCCs) has been recognized as a risk factor for acquiring gastrointestinal and respiratory infections
[1-3]. These infections can cause distress for both the children and their parents, incur costs for health care and parental work absence, and result in secondary transmission
[4-6]. Hand hygiene (HH) is a simple and effective measure to prevent infections
[7,8]. In the Dutch national HH guidelines for DCCs, the activities for which HH is indicated are outlined
[9]. However, compliance with HH guidelines is generally low; hands are adequately washed in Dutch DCCs in less than half of all HH opportunities (compliance 42%)
[10]. Several HH interventions have been developed to decrease infections in DCCs
[11-17]. However, these interventions show varying effects
[18] and are not developed according to a stepwise behavioral approach taking into account the underlying determinants of HH behavior
[19]. Interventions developed based on these determinants are more likely to be effective in the long term
[20]. A study on HH in hospitals has shown that interventions have more effect when a combination of multiple determinants is addressed
[21].

We assessed environmental and sociocognitive determinants of caregivers’ compliance with HH guidelines
[10,22], and have used the results of our studies to develop a multi-component intervention aiming to improve caregivers’ and children’s HH compliance and decrease infections among children attending DCCs. The intervention consists of the following four components: 1) products necessary for HH (i.e. dispensers and refills for paper towels, soap, alcohol-based hand sanitizer, and hand cream); 2) training to educate about the Dutch national HH guidelines; 3) two team training sessions aimed at goal setting and formulating specific HH improvement activities; and 4) reminders and cues to action (i.e. posters and stickers). The four components of the intervention together could potentially result in better HH compliance and fewer gastrointestinal and respiratory infections among children attending DCCs. However, before (inter)national dissemination of the intervention in other DCCs can be considered, it is necessary to evaluate the effectiveness of the intervention. The objective of this paper is to describe the design of a cluster randomized controlled trial to evaluate the effectiveness of the HH intervention.

## Methods/design

### Objectives and hypotheses

The study objective is to evaluate the effectiveness of a HH intervention in DCCs. Our hypotheses are that HH compliance of caregivers and children in intervention DCCs will be significantly higher than in control DCCs, and that children attending intervention DCCs will have significantly less gastrointestinal and respiratory infections than children attending control DCCs.

### Study design

The intervention will be tested in a two-arm cluster randomized controlled trial, to be conducted among 71 child DCCs; 36 intervention DCCs receive the intervention, while 35 control DCCs continue usual practice.

### Setting

The study will be conducted among DCCs in the Netherlands in the regions of Rotterdam-Rijnmond, Leiden and Gouda. This is a mixed urban–rural area with about 1.5 million inhabitants (of the total of approximately 17 million inhabitants in the Netherlands). In this area around 25,000 children attend about 390 DCCs (unpublished data 2008).

### Intervention development

Our previous studies concerning environmental and sociocognitive determinants of caregivers’ compliance with HH guidelines in DCCs
[10,22] were used to develop a multi-component HH intervention for DCCs. The intervention targets caregivers’ sociocognitive determinants such as guideline knowledge and awareness, perceived importance of performing HH, caregivers’ own perceived ability to perform HH when needed (i.e. perceived behavioral control), and habit (Table 
1). In addition, with the provision of HH products the intervention targets environmental determinants (Table 
1).

**Table 1 T1:** Intervention components and targeted determinants of hand hygiene (HH) behavior

**Intervention component**	**Targeted determinants of HH behavior**
1. Provision of HH products: dispensers and refills for paper towels, soap, alcohol-based hand sanitizer and hand cream	Environmental determinants, especially the availability of paper towels
2. Training to educate about the Dutch national HH guidelines; information booklet	Guideline knowledge and awareness, perceived HH importance
3. Two team training sessions aimed at goal setting and formulating specific HH improvement activities	Perceived HH importance, perceived behavioral control
4. Posters and stickers as reminders and cues to action	Guideline knowledge and awareness, habit

Our study on the environmental determinants of caregivers’ HH compliance showed that hands are most frequently washed when only paper towels are available compared to only fabric towels or a combination of both paper and fabric towels
[10]. Therefore, the intervention includes the provision of paper towel dispensers and refills. We also provide dispensers and refills for liquid soap, alcohol-based hand sanitizer, and hand cream to ensure that all necessary products for HH are available.

Our study on sociocognitive determinants demonstrated that the following determinants were related to HH compliance of caregivers: knowledge and awareness of the guidelines, perceived importance of performing HH, perceived behavioral control (i.e. caregivers’ own perceived ability to perform HH when needed), and habit
[22]. To improve knowledge and awareness of the HH guidelines and to increase perceived importance of HH, a one hour training session which incorporates the following topics was developed: transmission of infectious diseases, importance of HH at DCCs, the different activities outlined in the guidelines for which HH is indicated both for caregivers and children, and the techniques for performing HH using soap and water or alcohol-based hand sanitizer. The training session also includes an exercise using UV Glow Cream (Deb Benelux, Inc.) and a UV lamp to demonstrate the difference between quick and thorough hand washing. After the training session all participants, as well as caregivers who cannot attend, receive a booklet that outlines the content of the training about the HH guidelines.

To increase perceived behavioral control, two team training sessions were developed. The aim of these training sessions is to get team members to formulate team goals concerning HH and specific activities to improve HH of caregivers and children at their DCC. During the first training session, team members discuss current HH compliance, goal setting for future compliance, barriers and facilitators, and strengths of their team. During the second training session, which takes place about one month later, the interlaying period is reflected on and the following topics are discussed: rating of HH compliance of the team, improvements made so far, remaining difficulties and what is needed to address these, communication in case HH is not performed, and how to maintain the achieved results in the long term. The team training sessions are guided by trained coaches and are based on similar HH training sessions developed for Dutch hospitals
[23].

The intervention also includes reminders and cues to action to stimulate HH to become habitual behavior. For both caregivers and children a poster with the activities for which HH is indicated and a poster with the technique for adequate hand washing was developed, as well as reminder stickers. The posters and stickers were developed in collaboration with the department of Industrial Design of the Delft University of Technology in the Netherlands.

The intervention DCCs will be compared to control DCCs continuing usual practice. After data collection, the control DCCs will also be offered the intervention to motivate participation in the study.

### Participants

Of 390 DCCs, 122 participated in our previous study on environmental and sociocognitive determinants of caregivers’ compliance with HH guidelines
[10,22]. Of these 122 DCCs, 71 will participate in the trial to evaluate the effectiveness of the intervention. In Dutch DCCs, children aged three months to four years are cared for in groups or classes and each group of children has its own room where the daily activities take place (i.e. classrooms). In each participating DCC (both intervention and control), data will be collected in two of these groups, even if the DCC has more than two groups in total. Study participants will be caregivers (excluding interns) working in these two groups and children attending these groups. Inclusion criteria for the children are: aged at start of the trial between six months and 3.5 years; attending the DCC at least two days a week; intending to attend the DCC throughout the study period; and consenting Dutch speaking parents with access to email or regular post. Exclusion criteria for the children are: chronic illness or medication that would predispose them to infection; a sibling taking part in the trial (i.e. one child per family); and starting to attend the DCC after the start of the trial.

### Randomization

Stratified randomization is performed by assigning each DCC to one of six strata based on size (i.e. small < 46 children per day versus large ≥ 46 children per day) and geographic location (i.e. highly urban versus urban versus slightly/non-urban). DCCs are assigned to either intervention or control group by means of computer generation with a 1:1 ratio in each of the strata.

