### Data analyses

First, descriptive analyses will be performed to assess the effect of the intervention on observed HH compliance and on incidence of gastrointestinal and respiratory infections in children. Compliance with HH guidelines will be calculated by dividing the number of HH actions by the total number of opportunities for which HH is indicated according to the Dutch national guidelines. Incidence of gastrointestinal and respiratory infections will be calculated by dividing the number of illness episodes by the total number of days at risk.

To account for clustering of the data within caregivers/children and within DCCs, multilevel analyses will be performed. The effect of the intervention on observed HH compliance will be analyzed using multilevel logistic regression. Multilevel poisson regression will be used to analyze the effect of the intervention on incidence of gastrointestinal and respiratory infections in children. If necessary, baseline differences between intervention and control DCCs will be corrected for, as well as for possible confounders at the level of the DCCs, caregivers or children.

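### Minor: the models do not commit to the stratification factors (DCC size and urbanicity) and leave DCC-level adjustment to an if-needed rule that is unlikely to select them

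*Protocol article*

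**What the plan says.** Randomization section: "Stratified randomization is performed by assigning each DCC to one of six strata based on size" (below 46, or 46 and more, children per day) and on three classes of urbanicity. DCCs are then allocated "by means of computer generation with a 1:1 ratio in each of the strata". Study design section: "36 intervention DCCs receive the intervention, while 35 control DCCs continue usual practice".

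Data analyses section, on clustering: "To account for clustering of the data within caregivers/children and within DCCs, multilevel analyses will be performed". On the models: "The effect of the intervention on observed HH compliance will be analyzed using multilevel logistic regression", and "Multilevel poisson regression will be used to analyze the effect of the intervention on incidence of gastrointestinal and respiratory infections in children". On covariates: "If necessary, baseline differences between intervention and control DCCs will be corrected for, as well as for possible confounders", where the confounders may be at DCC, caregiver or child level.

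Neither size, urbanicity nor stratum is named as a model term. The article gives no figure for how strongly these factors relate to compliance or to infections.

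**The concern.** Stratified 1:1 allocation takes the between-stratum variation out of the true sampling variance of the arm difference. A model with arm and a DCC random effect, but no stratum terms, puts that variation back into the estimated DCC variance. The reported standard error is then larger than the real one, and the precision that stratification could have brought is not used.

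The adjustment rule makes this more than silence. It is triggered by baseline differences or by suspected confounding. Stratification keeps size and urbanicity close to balanced between arms, so they will rarely show a difference and can hardly confound. The two covariates with the clearest design reason to be in the model are the ones the rule is least likely to choose. It also leaves their inclusion to be decided after the data are seen.

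The outcomes to look at are the infection outcomes. They set the size of the trial, and the extra DCCs are only an allowance for dropout.

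**Working it through.** **What can be reproduced.** The article states no standard error or precision for the analysis, so the check starts from the sample sizes.

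*Compliance* (Sample size calculation: 30% versus 60%, 80% power, two-sided alpha 0.05, 60 opportunities per DCC, 10 DCCs per arm). Without clustering 42 opportunities per arm are needed. The plan has 10 × 60 = 600, a design effect of 600/42 = 14.3, hence an intracluster correlation (ICC) of (14.3 − 1)/59 = 0.225. Other versions of the two-proportion formula give 0.19 to 0.24. The article states no ICC, so this can only be back-solved.

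*Infections* (same section: 30 DCCs per arm, 10 children per DCC, six months). Person-years per arm: 30 × 10 × 0.5 = 150. Without clustering the need is (1.960 + 0.842)² × (λ0 + λ1)/(λ0 − λ1)².
- Gastrointestinal, 3 to 2.25 per year: 7.849 × 5.25/0.5625 = 73.3. Design effect 150/73.3 = 2.05.
- Respiratory, 9 to 7.65 per year: 7.849 × 16.65/1.8225 = 71.7. Design effect 150/71.7 = 2.09.

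*Dropout*: 60/0.85 = 71, against 70 planned and 71 in the trial.

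**Infections: effect of leaving the strata out.** Let f be the share of between-DCC variance that the strata explain (not in the article; assumed 10%, 20%, 30%). Let s be the share of total variance due to DCC clustering. If the whole excess over 1 in the design effect is DCC-level, s = (2.05 − 1)/2.05 = 0.51 (gastrointestinal) or (2.09 − 1)/2.09 = 0.52 (respiratory). This is an upper bound, because the article says that clustering within children is also in the calculation.

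- Overstatement of the standard error: r = 1/√(1 − f·s)
- Type I error without strata: 2(1 − Φ(1.96 r))
- Power without strata, if 80% was planned on the total DCC variance: Φ(0.842 r)
- Power with strata: Φ(2.802 r − 1.96)

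| f | r | Type I error without strata | Power without strata | Power with strata |
|---|---|---|---|---|
| 10% | 1.03 | 4.4% | 81% | 82% |
| 20% | 1.06 | 3.9% | 81% | 84% |
| 30% | 1.09 | 3.3% | 82% | 86% |

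The two infection outcomes agree to within rounding. At f = 0, r = 1 and nothing is lost.

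A second route gives a similar size. Ten children for half a year yield about 15 gastrointestinal or 45 respiratory episodes per DCC, so the Poisson variance of a DCC's log rate is 1/15 = 0.067 or 1/45 = 0.022. With a between-DCC coefficient of variation of 0.25 (assumed; variance 0.0625) and f = 20%, r = √[(0.067 + 0.0625)/(0.067 + 0.050)] = 1.05, or √[(0.022 + 0.0625)/(0.022 + 0.050)] = 1.08.

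**Compliance.** The ratio of standard errors without and with strata is √{[ICC + (1 − ICC)/60] / [ICC(1 − f) + (1 − ICC)/60]}. At ICC 0.20 it is 1.05, 1.11 and 1.18 for f = 10%, 20% and 30%.

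A simulation gives the consequence for the test: 71 DCCs, six roughly equal strata, 1:1 within strata, 60 opportunities each, ICC about 0.20, 4,000 replicates. It uses a linear analysis of DCC proportions, which approximates the planned multilevel model.

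| f | Type I error without / with strata | Power at log odds ratio 0.5, without / with |
|---|---|---|
| 0% | 4.7% / 4.9% | 60% / 60% |
| 10% | 4.1% / 4.8% | 61% / 63% |
| 20% | 3.4% / 4.8% | 61% / 66% |
| 30% | 2.0% / 5.2% | 64% / 72% |
| 50% | 0.9% / 5.0% | 67% / 84% |

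At the planned change from 30% to 60%, power was about 100% either way.

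**The case against.** The strongest reply is that this is an omission in a condensed article. The full list of model terms is commonly left to the full protocol or analysis plan, which are not shown. Size and urbanicity are DCC-level variables that could enter as possible confounders, and nothing in the text excludes them. This stands in part: a reader may not conclude that the analysis ignores the strata, or that they will never be adjusted for. But the article does more than stay silent. It states a conditional rule, and that rule is poorly suited to factors balanced by design.

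A reader might also infer a larger loss. Applying 1/√(1 − f) gives standard errors overstated by 5%, 12% or 20%, and Φ(2.80 − 1.96/√(1 − f)) gives power falling from 80% to 77%, 73% or 68%. The documents do not support either. The first formula leaves out the sampling variance within DCCs, which for the infection outcomes is about half of the total. The second assumes that the 80% was planned on the smaller, stratum-adjusted standard error. The sample size section says only that clustering is taken into account and credits no gain from stratification. If planning used the total DCC variance, power without strata does not drop below 80%; what is missed is a gain over the plan.

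It is also fair that the whole effect depends on the strata being prognostic, which the article does not show. If they are not, there is none. Any error is in the safe direction.

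**Conclusion.** The point holds as a minor one. Randomization is stratified on two factors that the stated models do not commit to, and the stated adjustment rule is unlikely to bring them in. If the factors are prognostic, omission gives somewhat wide confidence intervals and a conservative test, without bias and without inflation of the false-positive rate.

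For the infection outcomes the forgone power is about 1 to 4 points. This rests on the assumed range for f, on planning with the total DCC variance, and on the upper bound that all clustering is between DCCs; child-level clustering would make the effect smaller. For compliance the practical loss is negligible at the planned effect, since 71 DCCs take part and 20 were calculated as necessary. It would matter there only if the true effect were much smaller than planned and the strata were clearly prognostic.

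**What to change.** Add one sentence to Data analyses: DCC size (below 46 versus 46 or more children per day) and the three urbanicity classes are included as fixed effects in every logistic and Poisson model of the intervention effect, whatever the observed balance. Keep the conditional rule, if wanted, for other covariates only.

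The cost is three parameters (one for size, two for urbanicity), or five if all six strata are entered separately, with 71 DCCs. No new data are needed, because both factors are known for every DCC at randomization. In the simulation, including all six strata when they explained nothing cost no measurable power (60% either way).

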### Outcome measures

#### Primary outcome measure: observed HH compliance

The primary outcome measure is observed compliance of caregivers with HH guidelines. Compliance is defined as the number of HH actions divided by the total number of opportunities for which HH is indicated according to the Dutch national guidelines. According to these guidelines, HH is mandatory for caregivers before touching/preparing food, before caregivers themselves eat or assist children with eating, and before wound care; and after diapering, after toilet use/wiping buttocks, after caregivers themselves cough/sneeze/wipe their own nose, after contact with body fluids (e.g. saliva, vomit, urine, blood, or mucus when wiping children’s noses), after wound care, and after visibly soiled hands
[9]. For these HH indications it will be observed whether or not HH is performed. As observations cannot take place in the caregivers’ lavatory, HH after toilet use will only be observed after assisting a child with toilet use and not after toilet use by caregivers themselves. HH is defined as washing hands with water and soap followed by hand drying, or use of an alcohol-based hand sanitizer. An alcohol-based hand sanitizer cannot be used when hands are visibly soiled; in this case, hand washing with soap and water is required.

Although the primary outcome measure is HH compliance of caregivers, it will also be observed whether caregivers supervise children to wash their hands, because the HH indications outlined in the guidelines also apply to children
[9]. It will be observed whether caregivers supervise children to wash their hands before eating/preparing food, after toilet use, after playing outside, and after visibly soiled hands. Children should wash their hands with water and soap followed by hand drying. For babies and toddlers who cannot wash their hands themselves yet, caregivers can perform HH by using a wet cloth with soap on one side and only water on the other side
[9].

Compliance will be assessed with direct unobtrusive observation by trained observers before start of the intervention (T0) and one (T1), three (T2), and six (T3) months after start of the intervention. At each measurement time point (i.e. T0, T1, T2 and T3) the aim is to observe, during a single day in each DCC, three caregivers in the two groups participating in the study and to observe each caregiver for two hours. One observer will observe one caregiver at a time, as well as the children of which HH is supervised by that caregiver. Observations will take place during routine care activities in common rooms including the diaper-changing room, the kitchen and the indoor/outdoor playgrounds. The observers will collect data using personal digital assistants (PDAs) for electronic on-site data entry. Data will be collected using the World Health Organization HH observation method
[24], adapted for use in child DCCs.

